### 2.4. Randomization, Allocation Concealment and Blinding

A computer-generated random sequence with a 1:1 allocation ratio will be prepared by a statistician not involved in recruitment or outcome assessment. Sequentially numbered, opaque, sealed envelopes containing group assignments are used to ensure allocation concealment. After an eligible patient provides written informed consent and baseline data are collected, the educator opens the next envelope to reveal the assignment and deliver the appropriate intervention.

Outcome assessors and data analysts are blinded to group allocation. Complete blinding of outpatient clinicians is not feasible because some patients in the intervention group might spontaneously mention the planned CPET during follow-up, but clinicians are not informed of group assignment by the study team and are instructed not to seek this information.

### 2.5. Outcome and Covariates

The primary outcome is their attendance at the rehabilitation clinic within 30 days of hospital discharge. Attendance is defined as completion of at least one scheduled rehabilitation outpatient visit during this period at TCVGH. Attendance is verified via the hospital’s electric medical record system. Given the study’s focus on institutional workflow integration, visits to external facilities are not counted toward the primary endpoint to maintain data consistency.

Secondary outcomes include the following:Cardiac rehabilitation program participation: completion of a predefined early rehabilitation course within 12 weeks after discharge, defined as attending at least six supervised rehabilitation sessions.CPET completion: whether a CPET is ultimately performed during follow-up, irrespective of group.Safety: occurrence of adverse events potentially related to exercise or rehabilitation during the observation period, such as syncope during exercise sessions, sustained arrhythmias requiring urgent management, or emergency department visits or rehospitalization that related to therapeutic exercise

We will also collect the following covariates and potential determinants:Demographic factors—age, sex, body mass index (BMI).Socioeconomic and lifestyle factors—education level, employment and physical workload, physical activity level prior to ACS, and current smoking status.Social context—residential distance from the hospital and whether a family member accompanied the patient during hospitalization.Comorbidities—hypertension, diabetes mellitus, dyslipidemia, and renal impairment.ACS characteristics—ACS type based on electrocardiographic (ECG) findings (STEMI or NSTEMI), peak creatine kinase (CK) level, left ventricular ejection fraction (LVEF) by ECG, and hospitalization LoS.

In addition, to assess key behavioral constructs referenced in the theoretical framework, cardiac self-efficacy will be measured at baseline using the validated Cardiac Self-Efficacy Scale (CSES). The CSES is a disease-specific instrument designed to evaluate patients’ confidence in managing symptoms, maintaining physical function, and engaging in recommended health behaviors following cardiac events [42]. The questionnaire will be administered at the time of hospital discharge, prior to randomization. Higher scores indicate greater perceived self-efficacy related to cardiac disease management.

### 2.6. Sample Size Calculation

The sample size was estimated for the primary outcome of 30-day rehabilitation clinic attendance. Based on local and regional data indicating very low CR participation (<10%) after ACS [9,11,12,13]. Prior evidence demonstrates that low-cost, scalable interventions incorporating structured information delivery or “cue-to-action” strategies can produce absolute increases in cardiac rehabilitation participation of approximately 14–20% [43,44]. Therefore, we hypothesized that announcing a forthcoming CPET could increase this rate to 25%, corresponding to a 15% absolute improvement which is considered a conservative and clinically meaningful effect size, representing the minimum improvement likely to justify changes to standard discharge education and follow-up pathways. With a two-sided alpha of 0.05 and 80% power, this required approximately 100 patients per group (total 200). To allow for up to 10% attrition rate, we aimed to enroll at least 220 patients.

### 2.7. Statistical Analysis

All analyses will follow the intention-to-treat principle, and all randomized patients will be included in the primary analysis. Continuous variables are presented as means and standard deviations, and categorical variables as counts and percentages. Baseline characteristics are compared between groups using independent-samples *t* tests for continuous variables and chi-square tests for categorical variables.

For the primary outcome, participants who are lost to follow-up or whose attendance at the rehabilitation clinic cannot be confirmed through the electronic medical record system within the predefined 30-day window will be classified as non-attendees. The proportion of attendees between groups will be compared using the chi-square test, with crude odds ratios and 95% confidence intervals reported. A multivariable logistic regression model will then be fitted to estimate adjusted odds ratios (AORs) with 95% confidence interval for the effect of the intervention on attendance, adjusting for a prespecified set of clinically relevant covariates, including age, sex, ACS type (STEMI vs. NSTEMI), residential distance from the hospital, and baseline physical activity level, as these variables have been linked to cardiac rehabilitation referral/enrolment patterns or post-discharge health behaviors in patients with ACS [15,45,46].

In addition, a broader set of demographic, socioeconomic, clinical, and disease-related variables will be examined in secondary and exploratory analyses to further characterize factors associated with rehabilitation attendance: BMI; education level; employment and physical workload; smoking status; family accompaniment during hospitalization; comorbidities (hypertension, diabetes mellitus, dyslipidemia, and renal impairment); ACS-related characteristics, including peak CK level, LVEF, and LoS; and CSES score. Where appropriate, effect modification by key patient and clinical characteristics will be explored by including interaction terms between the intervention and selected variables.

Missing data in baseline covariates will be assessed for patterns and mechanisms. If the proportion of missing data is substantial, multiple imputation using chained equations will be applied as a sensitivity analysis, and results will be compared with complete-case analyses. All tests will be two-sided with a significance level of 0.05. Statistical analyses will be performed using SPSS (Version 29, IBM Corp., Armonk, NY, USA).

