### 3.2. Strength and Limitation

This study has several strengths. First, the randomized design minimizes selection bias, providing high-quality evidence regarding the causal effect of the announcement strategy. Furthermore, the intervention is low-cost and highly scalable, utilizing existing hospital resources rather than external funding or technology. At last, the inclusion of a determinant analysis allows for understanding of “who” responds to this incentive, aiding in the future personalization of care.

However, limitations are anticipated. As a single-center study, the generalizability of findings to rural hospitals or different healthcare systems may be limited. Additionally, due to the nature of the behavioral intervention, blinding of participants is not possible, which may introduce performance bias. Finally, the primary endpoint focuses solely on initial attendance; consequently, the study design does not enable the assessment of long-term adherence or hard clinical outcomes, such as re-hospitalization or mortality, despite existing evidence demonstrating favorable long-term outcomes with sustained participation in cardiac rehabilitation [21].

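### Effect modification is explored only through regression product terms, a ratio-scale measure, while the plan judges benefit in absolute attendance points; subgroup estimates of who responds should be shown on both scales.

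*Protocol article*

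**What the plan says.** Section 2.7 compares attendance with a chi-square test and a crude odds ratio, then fits a multivariable logistic model for an adjusted odds ratio. For subgroups it gives one method: "effect modification by key patient and clinical characteristics will be explored by including interaction terms between the intervention and selected variables". The sentence is qualified as applying where appropriate. It names no model, no scale and no list of modifiers. The adjustment covariates in the same section were chosen because "these variables have been linked to cardiac rehabilitation referral/enrolment patterns" or to behavior after discharge.

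Section 2.6 sets the worthwhile effect in absolute terms, a rise from about 10% to 25%, "corresponding to a 15% absolute improvement which is considered a conservative and clinically meaningful effect size", and describes it as "representing the minimum improvement likely to justify changes to standard discharge education and follow-up pathways".

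Section 3.2 lists as a strength that the determinant analysis will show who "responds to this incentive, aiding in the future personalization of care".

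**The concern.** Whether an effect differs between subgroups depends on the scale used. A logistic product term asks whether odds ratios differ. Deciding whom to target usually turns on how many extra patients attend per patient told, which is the scale on which section 2.6 justifies the trial. When control attendance differs between subgroups, equal odds ratios imply unequal absolute gains, equal gains imply unequal odds ratios, and the order of the subgroups can reverse. The plan's reason for choosing its covariates suggests that attendance will vary with at least some of them.

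At stake is the personalization message in section 3.2. A reader given only product terms could see no modification where absolute gains differ about two-fold, or could take the subgroup with the smaller gain for the better responder.

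**Working it through.** **Inputs from the protocol article.** Section 2.6: control attendance 10% (stated as below 10%; 10% follows from 25% minus 15 points), intervention attendance 25%, two-sided alpha 0.05, 80% power, about 100 per group. Section 2.7: odds ratios and logistic regression.

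**Assumed input.** The documents give no subgroup rates. I take two equal halves whose control rates average 10%: mainly 5% (L) and 15% (H), with 8%/12% and 3%/17% as a range.

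**1. The plan's own figure.** The pooled-variance two-proportion formula for 10% versus 25% gives 100 per group, and power at 100 per group is 0.802. The stated size reproduces. On the odds scale the same effect is (0.25/0.75)/(0.10/0.90) = 3.0.

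**2. Constant odds ratio, so the product term is null.** With p1 = 3·o/(1 + 3·o) and o = p0/(1 − p0):

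| Control rate | Intervention rate | Gain (points) |
|---|---|---|
| 3% | 8.5% | 5.5 |
| 5% | 13.6% | 8.6 |
| 10% | 25.0% | 15.0 |
| 15% | 34.6% | 19.6 |
| 20% | 42.9% | 22.9 |

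Between 5% and 15% the gains differ by a factor of 19.6/8.6 = 2.3, with no logistic interaction.

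**3. Constant gain of 15 points.** The odds ratio is 4.75 at a control rate of 5% (to 20%) and 2.43 at 15% (to 30%). The ratio is 2.43/4.75 = 0.51: a product term with no difference in absolute gain.

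**4. Reversed order.** H rises from 15% to 30%: +15 points, odds ratio (0.30/0.70)/(0.15/0.85) = 2.43. L rises from 5% to 15%: +10 points, odds ratio (0.15/0.85)/(0.05/0.95) = 3.35. H gains more in points, L more in odds.

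Holding the overall averages at 10% and 25%, the order reverses when the gain in L lies between these limits (the gain in H is 30 points minus that in L):

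| Control rates L/H | Gain in L with reversed order (points) |
|---|---|
| 8%/12% | 12.8 to 15 |
| 5%/15% | 9.2 to 15 |
| 3%/17% | 6.4 to 15 |

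The range shrinks as the control rates approach each other. With equal control rates both measures rise with the intervention rate alone, so the rankings agree.

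**5. What a trial of this size would show.** Simulation of 400,000 trials per scenario, 50 patients per arm-by-subgroup cell (200 in total). The product term is a Wald test with 0.5 added to cells; the additive test compares the two risk differences.

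| Scenario | Estimates of opposite sign | Product term p < 0.05 | Additive contrast p < 0.05 | Product term p < 0.05 and opposite-sign risk difference |
|---|---|---|---|---|
| Reversal (step 4) | 27.9% | 2.5% | 8.6% | 0 |
| Common odds ratio 3.0 (step 2) | 31.6% | 2.9% | 20% | 0 |
| Equal 15-point gains (step 3) | 23.4% | 5.2% | 5.4% | 0 |

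In the reversal scenario the log-odds estimate favors L, the half that gains less, in 62% of trials. The risk-difference estimate also favors L in 27.5%, from sampling error. For a further example at the plan's averages (5% to 18% and 15% to 32%, gains of 13 and 17 points), approximate interaction power is about 7% on the additive scale and 8% on the logistic scale.

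**The case against.** The case on the other side is substantial, and much of it stands.

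- **The sentence is brief and exploratory.** It names neither logistic regression nor the odds ratio, and an analysis plan could add absolute effects without contradicting it. This stands as a limit on weight. It does not remove the point: logistic regression is the only regression named in section 2.7, and the time-to-event models mentioned in the abstract would ordinarily give another ratio measure.
- **Logistic product terms are conventional, and section 3.2 does not define responding.** Also true. Section 2.6 uses absolute points for the overall effect, not explicitly for subgroups, and the determinant analysis may mean the wider study of factors associated with attendance. Using the absolute scale for targeting is an inference from section 2.6, though a natural one, since that is where the plan says what would justify a change in practice.
- **The subgroup rates are assumed.** Correct. The linkage stated in section 2.7 carries no magnitude.
- **Most sign disagreements are noise.** Correct. No simulated trial combined a significant product term with an opposite-sign risk difference, and the additive estimate often misranks subgroups as well.

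A reader might infer the stronger claim that the plan will declare the wrong subgroup, or that product terms are an error to be replaced. The documents do not support that. The analysis is described as exploratory, the subgroup rates are unknown, and at the trial's size and its 0.05 level the misdirected result is almost never declared.

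**Conclusion.** The point holds as a matter of scale and reporting. Product terms alone do not answer who gains most in attendance points, the currency of section 2.6. Under assumed control rates of 5% and 15%, a null product term is compatible with gains of 8.6 and 19.6 points, and the order of the point estimates can reverse. Both effects require control attendance to differ between subgroups and weaken as that difference narrows.

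The consequence is confined to the reading of exploratory estimates and to the personalization statement in section 3.2. The primary endpoint, its test and the sample size are untouched. With about 200 patients, confident subgroup conclusions are unlikely on either scale. This is a cheap improvement, not a defect that threatens the trial.

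**What to change.** Keep the product terms. In section 2.7 or the analysis plan, add for each modifier examined:

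- attendance by arm within each level;
- the risk difference at each level with a 95% confidence interval;
- the difference between those risk differences with a 95% confidence interval, for example by standardization from the same logistic model.

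State the scale in any sentence about who responds, look at the absolute differences before making a personalization statement, and label all of it hypothesis-generating.

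The cost is a few lines of text and a little more analysis, with no new data or patients. Recruitment is described as ongoing, so the wording can be settled before results are known. The downside is wide intervals, which should be shown as they are.

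### The adjusted logistic model of the primary outcome is by implication complete-case, so it can drop randomised patients whose arm and outcome are both known (minor)

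*Protocol article*

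**What the plan says.** All of the analysis text is in Section 2.7 of the protocol article.

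- **Analysis set.** "All analyses will follow the intention-to-treat principle, and all randomized patients will be included in the primary analysis".
- **Outcome.** Patients lost to follow-up, or whose attendance the medical record does not confirm "within the predefined 30-day window will be classified as non-attendees". No primary outcome can therefore be missing.
- **Analyses of the primary outcome.** A chi-square test with a crude odds ratio comes first. A logistic model follows, adjusted for age, sex, ACS type, residential distance and baseline physical activity. Neither is labelled the primary analysis.
- **Missing baseline covariates.** Patterns and mechanisms will be assessed. If the proportion missing is substantial, "multiple imputation using chained equations will be applied as a sensitivity analysis, and results will be compared with complete-case analyses". The word substantial is given no figure.

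Section 2.4 adds that baseline data are collected before the educator opens the allocation envelope.

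**The concern.** If imputation is the sensitivity analysis, the analysis it is set against is the main one, and the only one named is complete-case. When missingness is judged not to be substantial, no other method is offered at all.

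The plan closes off loss of patients on the outcome side by counting unconfirmed attendance as non-attendance. That leaves a missing baseline covariate as the only way out of the adjusted model. Patients with a known arm and a known outcome would be discarded for want of, say, a physical activity answer. This does not fit a rule that covers all analyses.

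Two things are at stake:

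- **Precision** of the adjusted odds ratio.
- **Comparability** of the crude and adjusted odds ratios. These differ to some extent even in the same patients, because one is conditional on covariates and the other is not. If they also come from different patients, a gap between them cannot be put down to adjustment alone.

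In addition, with no threshold, whether imputation is run at all can be settled after the data have been seen.

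**Working it through.** **Inputs from the protocol article**

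- Section 2.6: two-sided alpha 0.05 and 80% power, giving about 100 per group.
- Section 2.6: control participation from "local and regional data indicating very low CR participation (<10%) after ACS", and a hypothesis that the announcement would "increase this rate to 25%, corresponding to a 15% absolute improvement". The control rate is therefore 25% − 15 points = 10%.
- Section 2.4: 1:1 allocation.
- Section 2.6: "To allow for up to 10% attrition rate, we aimed to enroll at least 220 patients". That is 110 per arm (200 × 1.10 = 220). The Abstract gives 200 as the planned size, so both sizes are shown below.
- Share of patients with a missing covariate: not given. Assumed range 2% to 20%.

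**Step 1: reproduce the plan's own figure**

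Pooled two-proportion formula without continuity correction, with p1 = 0.10, p2 = 0.25, mean 0.175 and d = 0.15:

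n per arm = [1.960 × √(2 × 0.175 × 0.825) + 0.842 × √(0.10 × 0.90 + 0.25 × 0.75)]² / 0.15²
= [1.960 × 0.5374 + 0.842 × 0.5268]² / 0.0225
= (1.0532 + 0.4434)² / 0.0225 = 99.5, rounded up to 100.

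The stated 100 per group is reproduced.

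**Step 2: power with all patients kept**

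Power = Φ[(0.15 × √n − 1.0532) / 0.5268]

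- n = 100 per arm: Φ[(1.5000 − 1.0532) / 0.5268] = Φ(0.848) = 80.2%
- n = 110 per arm: Φ[(1.5732 − 1.0532) / 0.5268] = Φ(0.987) = 83.8%

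**Step 3: power on complete cases**

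The same formula is applied to the patients left, assuming equal loss in both arms.

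| Assumed share with a missing covariate | Left of 200 | Power | Left of 220 | Power |
|---|---|---|---|---|
| 0% | 200 | 80.2% | 220 | 83.8% |
| 2% | 196 | 79.4% | 216 | 83.1% |
| 5% | 190 | 78.1% | 209 | 81.9% |
| 10% | 180 | 75.9% | 198 | 79.8% |
| 20% | 160 | 70.8% | 176 | 74.9% |

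For scale: if only residential distance and physical activity were ever missing, each independently in 5% of patients, the complete share would be 0.95² = 0.9025. That is close to the 10% row.

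These figures are approximate for the adjusted model. They come from the unadjusted formula and ignore any gain from adjustment.

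**Step 4: which analyses are touched**

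- The chi-square test needs only arm and outcome. Both are known for every randomised patient, so it loses no one.
- The adjusted logistic model loses every patient with at least one of the five covariates missing.

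**The case against.** **The primary analysis is not shown to lose anyone.** A reader might infer that the trial's primary analysis drops randomised patients and so breaks the all-randomised rule. The document does not support that. It never calls the adjusted model primary. The chi-square comparison is listed first, the sample-size formula is a plain comparison of two proportions, and that comparison keeps everyone. The specific promise about the primary analysis can be met as written. This stands. The mismatch is with the wider statement that all analyses follow intention-to-treat.

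**No bias between arms is shown.** A reader might also infer bias, because patients who leave questionnaire items blank may be less likely to attend. Since baseline data precede the opening of the envelope, missingness cannot be caused by the arm. Patients kept on a pre-randomisation feature still form a randomised comparison. This also stands, although the estimate then describes only patients with complete baseline data.

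**The loss may be small and already covered.** Age, sex and ACS type are routine inpatient data. Because the outcome is complete by rule, the 10% attrition allowance is free to absorb covariate loss, and 10% missing at 220 still leaves 79.8%. This stands and limits the severity.

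**This is detail for an analysis plan.** It holds in part. A numerical threshold could well be given there, and complete-case is an inference here, since no sentence names it as the main method. But the article does fix the role of imputation as a conditional sensitivity analysis, and that is a stated choice with a better alternative.

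How unstable angina fits an ACS-type covariate coded as STEMI versus NSTEMI is a question of coding. It is separate from this point.

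**Conclusion.** The point holds as a minor one. For the adjusted logistic model of the primary outcome, the stated handling of missing covariates implies complete-case analysis. That does not fit the intention-to-treat statement covering all analyses, and it gives up patients who could be kept.

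The cost is some precision, and an adjusted odds ratio that may rest on fewer and different patients than the crude one. At the enrolment target of 220, the loss is about 2 points of power at 5% missing (83.8% to 81.9%) and 4 points at 10% (83.8% to 79.8%). With 200 patients there is no margin, and the same shares give 78.1% and 75.9%.

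These sizes rest on assumed missingness, equal loss in both arms and an unadjusted power formula. If the covariates prove complete, nothing is lost.

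**What to change.** In Section 2.7, or in the analysis plan:

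1. State that the adjusted model includes all randomised patients, whatever the amount of missing covariate data.
2. Name the method for the main adjusted analysis. One option is to fill in missing baseline covariates blind to arm and outcome: the mean for a continuous covariate, or a missing category or indicator. The other is to use multiple imputation as the main adjusted analysis.
3. Make complete-case the sensitivity analysis.
4. Delete the condition that missingness be substantial, so that the method no longer depends on a judgement made after seeing the data.

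The cost is a sentence or two and slight extra programming, plus reliance on a simple imputation model. Section 2.1 says recruitment is ongoing, so the change can be made before analysis.
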